## Abstract

**Background:**

Physical activity shows potential in combating the poor outcomes associated with depression in older people. Meta-analyses show gaps in the research with poor trial design compromising certainty in conclusions and few programmes showing sustained effects.

**Methods/design:**

The Depression in Late Life: an Intervention Trial of Exercise (DeLLITE) is a 12 month randomised controlled trial of a physical activity intervention to increase functional status in people aged 75 years and older with depressive symptoms. The intervention involves an individualised activity programme based on goal setting and progression of difficulty of activities delivered by a trained nurse during 8 home visits over 6 months. The control group received time matched home visits to discuss social contacts and networks. Baseline, 6 and 12 months measures were assessed in face to face visits with the primary outcome being functional status (SPPB, NEADL). Secondary outcomes include depressive symptoms (Geriatric Depression Scale), quality of life (SF-36), physical activity (AHS Physical Activity Questionnaire) and falls (self report).

**Discussion:**

Due to report in 2008 the DeLLITE study has recruited 70% of those eligible and tests the efficacy of a home based, goal setting physical activity programme in improving function, mood and quality of life in older people with depressive symptomatology. If successful in improving function and mood this trial could prove for the first time that there are long term health benefit of physical activity, independent of social activity, in this high risk group who consume excess health related costs.

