### Developing a programme

We adapted an existing exercise programme, the *Otago Exercise Programme (OEP)*, which has been shown to improve function and reduce the risk of falls among older adults [33]. The OEP is a set of individualised progressive lower leg strengthening and balance retraining exercises coupled with regular walking. We have enhanced the OEP regimen with two additional home visits and additional exercises focussed on upper limb strengthening. Two further adaptations were added to encourage participation and sustainability considering the target group (older people with depression) including goal setting and involvement of a social 'coach' or person to complete activities with the older person.

Increasing depressive symptoms lead to a decline in physical performance [16]. To improve function for people with depression is likely to enhance independence and improve quality of life for the participant. Whilst depression is a relevant outcome in itself, reducing the disability and dependency related to that diagnosis are key aims and outcome measures for this trial.

We sought to develop a sustainable programme designed to be delivered at home and test it in a rigorous trial addressing appropriate description of levels of depression at entry, using a control group receiving similar amounts of attention to control for the social impact of activity training and with long term follow up to establish potential long term effectiveness and sustainability of activity.

In this study we aimed to assess the impact in depressed older people of this home-based physical activity programme, incorporating goal setting, in improving functional status, depressive symptoms and quality of life. This paper describes the study protocol and recruitment for the Depression in Late Life: an Intervention Trial of Exercise (DeLLITE).

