#### Intervention Group

Intervention group participants were visited at home by a trained intervention nurse and instructed in an individualised home-based physical activity programme. The programme was based on the participant setting a functional goal (e.g. being able to prune the roses again or able to do a load of washing independently) and the nurse completing a functional assessment and designing an individualised programme based on the functioning needed for the goal [36]. The programme incorporated the activities of the Otago Exercise Programme[33] with regular walking three times per week, progressive resistance training of the upper and lower limbs using weights and balance retraining using progressive balance exercises. Adherence to activities was promoted by involvement of a companion, already known to the participant, so that walking was accompanied and exercises encouraged. The walking companion may have been a friend, relative, carer, or a community volunteer where this was available.

The intervention nurse made eight home visits, six in the first two months, a seventh at three months and a final visit at six months. To ensure adherence and progression of activity fridge calendars were used by the intervention group participants to record the number of exercise episodes and walking frequency. These were continued and either posted back or collected by the intervention nurse throughout the year of follow up to encourage and measure adherence.

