#### Control Group

Control group participants received social visits from the social visitor with conversation based around current social activities and social networks. These visits were time-matched to the intervention group visits and eight visits were received in total over 6 months. Each visit took half to one hour. This was used to control for the potential social aspect of being visited by the intervention nurse. This amount of social contact has the potential to improve mood and we wished to establish the effect of activity independent of the social contact of the intervention nurse.

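### The abstract claims a benefit of activity independent of social activity, but the control arm matches only the home visits; the companion and year-long calendars are described for the intervention arm alone

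*Protocol article*

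**What the plan says.** The abstract's Discussion paragraph states what a positive result could prove: that "there are long term health benefit of physical activity, independent of social activity". In the Background, Developing a programme says the control group receives similar attention so that the social impact of the activity training is controlled for.

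The Control Group section is narrower. Of the social visits it says: "This was used to control for the potential social aspect of being visited by the intervention nurse". It adds that the aim is to separate activity from the nurse's social contact.

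The intervention contains more than exercise and nurse visits. Developing a programme lists, as a deliberate addition, "involvement of a social 'coach' or person to complete activities with the older person". The Intervention Group section says: "Adherence to activities was promoted by involvement of a companion, already known to the participant, so that walking was accompanied and exercises encouraged". On who this was: "The walking companion may have been a friend, relative, carer, or a community volunteer where this was available". The same section says that "fridge calendars were used by the intervention group participants to record the number of exercise episodes and walking frequency", and then: "These were continued and either posted back or collected by the intervention nurse throughout the year of follow up to encourage and measure adherence". The Control Group section describes neither a companion nor a calendar.

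**The concern.** To show an effect of activity independent of social activity, the arms must be alike in social activity, or differ in it only as a consequence of being active. Here a social component is part of what one arm is assigned. The article treats such components as capable of affecting outcome: its Social Participation section ties social support to long-term wellbeing, and its Control Group section says that contact on the scale of the visits could improve mood. That reasoning is why the visits were matched, and it applies equally to a companion.

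What is at stake is the interpretation of a positive result. Reported in the abstract's terms, it would tell readers that companionship had been ruled out as an explanation, which the comparison cannot do. A second, smaller issue concerns the words on long-term benefit. Outcome Measures labels month 6 the end of the intervention, yet an adherence prompt continues to month 12 in one arm.

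**Working it through.** No sample-size or power figure bears on this point. The check sets the arms side by side.

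**Visits.** "The intervention nurse made eight home visits, six in the first two months, a seventh at three months and a final visit at six months": 6 + 1 + 1 = 8 over 6 months. The Control Group section also gives eight, time-matched, over 6 months. The visit schedule is therefore balanced, as the article says.

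**All described components**

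| Component | Intervention | Control | Matched? |
|---|---|---|---|
| Staff home visits, months 0–6 | 8 | 8 | Yes |
| Exercise and walking programme | Yes | No | No (the intended contrast) |
| Goal setting | Yes | No | No |
| Companion or social coach | Yes | None described | No |
| Visit talk centred on social activities and networks | None described | Yes | No |
| Adherence calendars, months 0–12 | Yes | None described | No |

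**What the difference contains.** Assume for simplicity that effects add. Write V for the effect of being visited, E for exercise, G for goal setting, C for the companion, K for the calendars, and S for the social content of the control visits.

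- Intervention arm: V + E + G + C + K
- Control arm: V + S
- Difference: E + G + C + K − S

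Matching the visits removes V. That is the property the Control Group section claims, and the design has it. The abstract's claim needs the social terms, C − S, to be absent as well. Nothing in the design removes them.

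**Sign and size of C − S.** C could be small if the companion was a spouse or carer whose company the participant already had. S could be positive if talking about networks led controls to do more socially. The article gives no figure for either, so neither the sign nor the size follows from it.

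**Could analysis separate them?** Whether and how often a companion took part is determined after randomisation and in one arm only. Adjusting for it would not give a randomised contrast for activity alone. This limit comes from the design, so it does not depend on an analysis plan that is not shown.

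**Month 12.** After month 6 neither arm has scheduled programme visits, but K continues in the intervention arm. The 12-month difference is therefore one with adherence support still running in that arm.

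**The case against.** The strongest reply is that the body of the article already makes the narrower claim. Methods (Design) sets a home-based activity programme against a social intervention, the companion is openly listed as part of the programme, and the Control Group section confines itself to nurse contact. The fault then lies in one conditional sentence of the abstract, on which no outcome or analysis rests. This largely stands and is why the remedy is only wording. It does not dispose of the point: the abstract states what the trial would prove, and Developing a programme also describes the control too broadly.

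It is also fair that the control visits were not socially neutral, and that the primary outcome is function. The argument is weaker for the observed SPPB than for mood and quality of life, which are secondary. The abstract's sentence does, however, name mood as well as function.

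Three stronger readings are tempting, and the article does not support them.

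- A reader might count contacts: three walks a week over 26 weeks is 78, against 8 matched visits, so that matching covers 8/86 = 9% of contacts. That assumes every walk was accompanied. At 25% accompanied the share is 8/27.5 = 29%, and at 10% it is 8/15.8 = 51%. The rate is not reported, walks with a familiar person need not be extra contact, and walks and visits are not equal units. The share measures no bias.
- A reader might infer a year of personal contact through the calendars. They could simply be posted back, and they also served to measure adherence.
- A reader might infer that the article promises an effect persisting after all support has stopped. It says long term and seeks sustainability; it does not say that.

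**Conclusion.** The point holds as a mismatch between claim and design. The eight matched visits support a conclusion about the programme beyond visit contact. They do not support one about activity independent of social activity. The problem is greatest for mood and quality of life. No numerical size can be given, and the direction of any net social imbalance is open.

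This rests on two assumptions: that the article describes all the programme components in each arm, so that controls had no companion or calendar, and that companions were used to some extent in the intervention arm. It would be wrong to conclude that the trial is invalid or its estimate biased for the comparison actually randomised. The contrast between the two packages is sound; only its attribution to one ingredient is not.

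**What to change.** 1. In the abstract, delete the clause on independence from social activity. State the conclusion, in line with the Control Group section, as the effect of the whole activity programme (exercise, goal setting, companion and calendar) over and above time-matched social home visits.
2. In Developing a programme, describe the control group as controlling for the social contact of the home visits.
3. Describe the 12-month result as obtained with adherence calendars continuing in the intervention arm.

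The cost is a few sentences and a narrower claim. Sample size, outcomes and analysis do not change. New data collection is not asked for: recruitment closed in January 2007, so added questions could cover only part of the follow-up. Nor is a control-arm calendar, which could itself prompt activity and dilute the contrast.

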**Trial registration:**

Australian and New Zealand Clinical Trials Register ACTRN12605000475640

## Background

Depression is a common condition in older people, affecting between 17 and 30% of community dwellers over the age of 65 years [1]. Depression can be associated with significant disability, adverse health outcomes, poor quality of life and excess mortality [2] and thus is a significant concern for older people.

Treatment of depression in older people has limitations. Pharmaceutical interventions have potential side effects and potentiate drug interactions which can be particularly hazardous in older people. Psychological therapies [3] are limited by their availability in many settings, and for many therapies, the evidence base for their impact in elderly populations is lacking. Therefore, there is a need to develop and test new treatments and ways of enhancing existing treatments for depression in older people to prevent the morbidity and mortality afforded by this serious condition.

### Depression and physical activity

Recent randomised controlled trials and meta-analysis have demonstrated the antidepressant effect of physical activity and exercise in older adults with clinical depression [4-6]. Different forms of physical activity have been studied. While several trials have shown that progressive resistance training delivered over 10 weeks improves mood in the short term [7], other trials have tested the benefits of aerobic activity [4,5,8] and moderate activity such as walking [9].

The frequency of activity may be more important than the intensity of sessions and the longer the intervention is maintained the greater the benefit [10]. Both moderate and vigorous levels of activity show efficacy in reducing depressive symptoms [11] and progressive resistance training is equally as successful as aerobic activity [10].

Meta-analyses however have been critical of the quality of trials [12] with commonly identified difficulties being a lack of standard diagnostic process for identifying depression in participants, short follow up periods, control groups that do not control for the attention of the exercise facilitator and small effect sizes [11,12]. There are few programmes that suggest ease in widespread dissemination.

### Depression and functional status

The disability from depression has been shown to be greater than that from major chronic medical conditions [13-15]. The greater the depressive symptoms, the greater the decrease in level of function [16,17]. Functional limitation has been shown to predict a variety of adverse outcomes including depression, rest home admission and mortality [16,17] and higher rates of depression are associated with being home bound [18], socially isolated [19] and medically unfit [20].

Physical disability is also a risk factor for the development of depression [21] supporting the hypothesis that disability and depression are interrelated, creating a spiral of increasing psychological and physical decline [22]. Physical activity can alleviate the development of disability [23], however, sustainability is key and people with poor socialisation patterns and depression are difficult to engage in new activity programmes [24].

### Social Participation

Social participation and social support networks are paramount to long term positive outcomes and psychological wellbeing for older people [25,26]. A social context for physical activity and activity of a moderate rather than vigorous intensity promotes participation among older people [27]. Sedentary older people are more socially isolated than those participating in regular physical activity [28]. Continued support is important to interventions achieving long lasting change in exercise behaviour [29]. It is clear that social issues contribute to depression [30] and the importance of caregivers and other social supports in successful ageing for older people is well understood [31]. A social context to the physical activity intervention may be important to promote participation of older people. As depression is associated with poor participation in physical activity and health promotion programmes [32] increased effort in recruitment will be needed to engage older people with depression.

### Developing a programme

We adapted an existing exercise programme, the *Otago Exercise Programme (OEP)*, which has been shown to improve function and reduce the risk of falls among older adults [33]. The OEP is a set of individualised progressive lower leg strengthening and balance retraining exercises coupled with regular walking. We have enhanced the OEP regimen with two additional home visits and additional exercises focussed on upper limb strengthening. Two further adaptations were added to encourage participation and sustainability considering the target group (older people with depression) including goal setting and involvement of a social 'coach' or person to complete activities with the older person.

Increasing depressive symptoms lead to a decline in physical performance [16]. To improve function for people with depression is likely to enhance independence and improve quality of life for the participant. Whilst depression is a relevant outcome in itself, reducing the disability and dependency related to that diagnosis are key aims and outcome measures for this trial.

We sought to develop a sustainable programme designed to be delivered at home and test it in a rigorous trial addressing appropriate description of levels of depression at entry, using a control group receiving similar amounts of attention to control for the social impact of activity training and with long term follow up to establish potential long term effectiveness and sustainability of activity.

In this study we aimed to assess the impact in depressed older people of this home-based physical activity programme, incorporating goal setting, in improving functional status, depressive symptoms and quality of life. This paper describes the study protocol and recruitment for the Depression in Late Life: an Intervention Trial of Exercise (DeLLITE).

## Methods

### Design

A randomised controlled trial design was used to test the efficacy of a home based physical activity programme in improving health outcomes in depressed older people compared with a control group receiving a social intervention.

#### Participants

Community dwelling adults aged 75 years and older from Auckland, New Zealand, general practices were identified through practice-based computer systems. Exclusion criteria included: living in residential aged care, severe dementia, terminal illness, not able to communicate in English or unstable medical condition such that participation in a physical activity programme was unsafe (as judged by their general practitioner (GP)).

#### Recruitment (see Figure 1)

**Figure 1 F1:**
[figure not shown]
Recruitment Flowchart and Identification of Eligible Population.

A random sample of general practitioners from three large urban suburbs in the Auckland region were approached in random order with a faxed invitation. Interested doctors were visited by a research nurse, the study explained and a list of all patients 75 years and older generated. The GP and practice staff perused the list to exclude patients who were not community-dwelling, who had dementia or an unstable medical condition or who would not be able to participate in a physical activity programme. An invitation letter, signed by the GP was mailed to the patients with a brief depression screen comprising three questions [34]:

1) During the past month have you often been bothered by feeling down, depressed or hopeless?

2) During the past month have you often been bothered by having little interest or pleasure in doing things?

3) Answer if you responded 'yes' to 1. or 2: Is this something with which you would like help?

Scores of two yes's of a possible three were considered sufficient for inclusion. Completed questionnaires were returned in a reply paid envelope with an indication of whether the potential participant was interested in hearing more about the study. Those who did not send back the screening questionnaire were contacted by telephone by a researcher and the three question depression screen administered.

Those who were interested and who fulfilled criteria were phoned by a research nurse and asked the following medical questions:

1) Have you suffered from a heart attack in the past 6 months?

2) Have you suffered from a stroke in the past 6 months?

3) Do you suffer from:

a. Ongoing chest pains?

b. Dizziness?

c. Fainting attacks?

d. Shortness of breath that stops you from walking across the room?

If the potential participant 'failed' the medical screen, the researcher faxed the GP a request for medical clearance.

Recruitment processes were undertaken over 10 months from March 2006-January 2007 to allow the intervention to be delivered during all seasons as seasonal variation in mood status may impact results [35]. Written informed consent was obtained in person during a home visit.

#### Randomisation and Blinding

A researcher at a distant site allocated individuals to each group according to a computer-generated randomisation schedule. Couples were given the same allocation to avoid cross contamination. Assessors remained blind to allocation of randomisation at each measurement point.

#### Intervention Group

Intervention group participants were visited at home by a trained intervention nurse and instructed in an individualised home-based physical activity programme. The programme was based on the participant setting a functional goal (e.g. being able to prune the roses again or able to do a load of washing independently) and the nurse completing a functional assessment and designing an individualised programme based on the functioning needed for the goal [36]. The programme incorporated the activities of the Otago Exercise Programme[33] with regular walking three times per week, progressive resistance training of the upper and lower limbs using weights and balance retraining using progressive balance exercises. Adherence to activities was promoted by involvement of a companion, already known to the participant, so that walking was accompanied and exercises encouraged. The walking companion may have been a friend, relative, carer, or a community volunteer where this was available.

The intervention nurse made eight home visits, six in the first two months, a seventh at three months and a final visit at six months. To ensure adherence and progression of activity fridge calendars were used by the intervention group participants to record the number of exercise episodes and walking frequency. These were continued and either posted back or collected by the intervention nurse throughout the year of follow up to encourage and measure adherence.

